# The efficacy and stability of an information and communication technology-based centralized monitoring system of adherence to immunosuppressive medication in kidney transplant recipients: study protocol for a randomized controlled trial

**DOI:** 10.1186/s13063-017-2221-z

**Published:** 2017-10-16

**Keywords:** Information and communication technology, Adherence, Kidney transplantation

## Abstract

**Background:**

Immunosuppression non-adherence in kidney transplant recipients (KTRs) not only increases the risk of medical intervention due to acute rejection and graft loss but burdens the socioeconomic system in the form of increased healthcare costs. An aggressive preemptive effort by healthcare professionals, geared to ensure adherence to immunosuppressants in KTRs, is significant and imperative.

**Methods/design:**

This study was designed as a prospective, open-label, multicenter, randomized controlled study aimed at evaluating the efficacy and stability of an information and communication technology (ICT)-based centralized monitoring system in boosting medication adherence in KTRs. One hundred fourteen KTRs registered throughout the year 2017 to 2018 are randomized into either the ICT-based centralized home monitoring system or to ambulatory follow-up. The planned follow-up duration is 6 months. The ICT-based centralized home monitoring system described consists of a smart pill box equipped with personal identification system, a home monitoring system, an electronic Case Report Form (eCRF) system, and a comprehensive clinical trial management system (CTMS). It alerts both patients and medical staff with texts and pill box alarms if there is a dosage/dosing time error or a missed dose. Medication adherence and transplant outcomes for the follow-up period are compared between the two groups, while patient satisfaction as well as the stability and cost-effectiveness of the ICT-based monitoring system are to be evaluated.

**Discussion:**

This on-going study is expected to determine if consistent use of the ICT-based centralized monitoring system described could maximize mediation adherence and subsequently enhance transplant outcomes in KTRs. Further, it would lay the foundation for successful implementation of this ICT-based monitoring system for effective management of medication adherence in KTRs.

**Trials registration:**

ClinicalTrials.gov, Identifier: NCT03136588. Registered on 20 April 2017.

**Electronic supplementary material:**

The online version of this article (doi:10.1186/s13063-017-2221-z) contains supplementary material, which is available to authorized users.

## Background

Regular administration of immunosuppressants is critical in kidney transplant recipients (KTRs) to reduce the risk of acute rejection and enhance graft survival. A previous study has reported that the major cause of graft loss is antibody-mediated rejection which was shown to be associated with impaired adherence to immunosuppressants [1]. Non-adherence is not only medically significant, being responsible for acute rejection [2, 3] and graft loss [4], but also has wide socioeconomic implications resulting from increased healthcare costs [5] for additional hospitalization, acute rejection treatment, and re-dialysis. Given the multifaceted risk associated with immunosuppression non-adherence in KTRs, aggressive intervention by healthcare professionals to ensure adherence is imperative.

Conventional ways of assessing drug adherence include blood drug level measurement, pill counts, patient interview/use of questionnaires, and electronic monitoring. Blood drug concentration provides direct evidence, but is rarely useful due to inter-individual variability in pharmacodynamics [6]. There is also risk of errors due to the white-coat compliance where drug adherence improves abruptly for the 5 days immediately preceding a physician visit [7]. Pill count is even less reliable, barely providing information on dosing time compliance. While easy to implement, patient interview/questionnaires also pose reliability issues. Electronic monitoring has been regarded as the standard assessment of adherence [8]. It keeps records of the date/time when patients open the pill box, and the computer-connected data is downloadable and analyzable. Though the simple date/time data does not really ensure whether medication is actually taken, electronic monitoring is still considered the most reliable [9]. Henriksson et al. have conducted a study where the date/time record of immunosuppression administration in KTRs was transmitted via web-based reporting tools. Subjects were randomized to the electronic adherence monitoring system or the control system. The prospective study with 1-year follow-up has demonstrated a greater adherence with a lower rejection rate in the electronic monitoring group than in the control group [10]. In a more recent randomized clinical trial, Reese et al. have investigated KTRs who had been given pill bottles to demonstrate that the greatest adherence was achieved in those who received provider notification together with customized reminders [11].

The present clinical trial aims to investigate efficacy and stability of continuous adherence management in KTRs by means of an information and communication technology (ICT)-based centralized clinical trial monitoring system.

## Methods/design

### Study objectives

Assuming unintended forgetfulness of KTRs to take immunosuppressants oftentimes, the study seeks to identify how continuous adherence management with the ICT-based centralized clinical trial monitoring system affects drug adherence and how improved adherence is associated with therapeutic drug concentrations as well as immunological and clinical outcomes. It also aims to determine patient satisfaction with the ICT-based centralized monitoring system as well as its stability and cost-effectiveness.

### Study design

This study has a multicenter, open-label, prospective, randomized controlled trial (RCT) design. One hundred fourteen KTRs who fill out the Informed Consent Form are registered and randomized 1:1 into the ICT-based centralized clinical trial monitoring group (*n* = 57) or the ambulatory follow-up group (*n* = 57). The planned follow-up duration is 6 months (Fig. 1). The ICT-based centralized clinical trial monitoring group is given a smart pill box equipped with a personal identification system. Fingerprint registration is required in advance, so that it would be used for authentication before each use of the smart pill box later. The adherence-related information obtained from the pill box is saved, monitored, and sent out via a home monitoring system. Of the home monitoring system data, those necessary for the clinical trial are extracted and incorporated into the electronic Case Report Form (eCRF) system. All data is consolidated and managed within the comprehensive clinical trial management system (CTMS). In the ICT-based, centralized clinical trial monitoring group, feedback is sent to both patients and medical staff in the form of texts and pill box alarms if there is a dosage/dosing time error or a missed dose.

**Fig. 1 Fig1:**
[figure not shown]
ICT-based study design. *ICT* information and communication technology, *R* randomization, *S* screening, *W* week

Both groups are to make six office visits after randomization at 4, 8, 12, 16, 20, and 24 weeks. Each visit requires measurement of blood drug level, creatinine level, and estimated glomerular filtration rate (eGFR). Serum BK virus is assessed at 12 weeks, and panel reactive antibody (PRA) at 24 weeks. Both groups keep a drug administration diary that specifies date, whether a dose is taken or not, dosing time, and dosage. At each visit, subjects go over the diary with investigators and fill out a questionnaire using the Modified Morisky Adherence Scale [12]. The ICT-based centralized clinical trial monitoring group completes a patient Satisfaction Questionnaire developed by the ICT Clinical Trial Support Center at 4 and 24 weeks. The system Satisfaction Questionnaire can be found in Additional file 1. The protocol flow is shown in detail in the Standard Protocol Items: Recommendations for Interventional Trials (SPIRIT) figure in Fig. 2. A SPIRIT Checklist is provided in an Additional file 2.

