### Questionnaires

Participants in both groups will complete the Modified Morisky Adherence Scale [13] and the Belief about Medicine Questionnaire—general (BMQ-G) [14]. We aim to investigate the patients’ level of trust on their prescriptions and their perception of medication use.

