### Primary outcomes

The primary outcome in this trial is adherence to medication. Both in the ICT-based centralized clinical trial monitoring group and the control, pill counts are done at 4, 8, 12, 16, 20, and 24 weeks of follow-up. Multiple items of adherence – dose-taking compliance, dose-frequency compliance, dose-interval compliance, and drug holidays – are assessed based on the smart pill box data in the ICT-based centralized monitoring group and the drug administration diary in the ambulatory follow-up group, respectively. In the ICT-based centralized monitoring group, three types of immunosuppressants—tacrolimus, mycophenolic acid, and steroids—are placed in a single bag, which is then placed inside a smart pill box. The patient’s medication usage is assessed based on the perceived weight of the leftover medications in the bag. On the basis of this weight information, we can identify the type and dose of medications that the patient has ingested, and calculate the adherence. Each item of adherence is listed below [15]:Dose-taking compliance = the number of pills taken over a certain time period/the number of pills prescribed over the same period × 100%Dose-frequency compliance = the number of days of correct daily dosing frequency over a certain time period/the number of days over the same period × 100%Dose-interval compliance: the number of correct dosing interval over a certain time period/the number of days over the same period × 100%.A correct dosing interval is defined with a ± 25% margin (in this trial, medication is taken twice a day, with a dosing interval of 12 h. Allowed dosing interval is thus ranged from 9 to 15 h)Drug holidays = the number of days without dose taking/the number of days over the same period × 100%Medication possession ratio = the sum of the days’ supply for all fills of a given drug in a particular time period/the number of days in the time period × 100%

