### Secondary outcomes

The secondary outcomes in this trial include blood drug levels, immunological outcome, clinical outcome, patient satisfaction with the system, and the system stability and cost-effectiveness. The trough levels of tacrolimus and mycophenolic acid, creatinine level, and eGFR are measured at 4, 8, 12, 16, 20, and 24 weeks of follow-up. PRA is assessed at baseline and 24 weeks, and serum BK virus at 12 weeks. For clinical outcome evaluation, biopsy-proven acute rejection (BPAR) and graft loss developing during the follow-up are monitored. The patient Satisfaction Questionnaire is filled out at 4 and 24 weeks in the ICT-based centralized clinical trial monitoring group in order to assess how well the patients are satisfied with the system-enabled adherence management. The malfunction rate of the ICT-based centralized monitoring system is checked as well as any discrepancy between the smart pill box record and the patient-kept drug administration diary. Information about patients’ medication use sent to the ICT-based monitoring system is compared with the daily records of medication use written by the patients (type of medications used, number of pills ingested, and time of ingestion) to assess how closely they match. Stability is measured by using the following equation:$$ \frac{\mathrm{Number}\  \mathrm{of}\  \mathrm{pills}\  \mathrm{taken}\  \mathrm{over}\ \mathrm{a}\ \mathrm{certain}\  \mathrm{period}\  \mathrm{according}\  \mathrm{to}\  \mathrm{the}\ \mathrm{ICT}\hbox{-} \mathrm{based}\  \mathrm{centralized}\  \mathrm{monitoring}\  \mathrm{system}}{\mathrm{Number}\  \mathrm{of}\  \mathrm{pills}\  \mathrm{prescribed}\  \mathrm{over}\  \mathrm{the}\  \mathrm{sampling}\  \mathrm{period}\  \mathrm{according}\  \mathrm{to}\  \mathrm{the}\  \mathrm{daily}\  \mathrm{record}\  \mathrm{of}\  \mathrm{medication}\ \mathrm{use}}\times 100\%. $$

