### Process evaluation

The Reach, Effectiveness, Adoption, Implementation, and Maintenance (RE-AIM) framework [16] will be used in order to evaluate translatability and feasibility of ICT-based centralized monitoring system. Reach is defined as the absolute number and participation rate of eligible KTRs who participate in the ICT-based RCT. Effectiveness is defined as the improvement in adherence to immunosuppressive medication in KTRs. Adoption is defined as the absolute number, proportion, and representativeness of hospitals that are willing to participate in the ICT-based RCT. Implementation is defined as the percentage of KTRs who follow the ICT-based centralized monitoring system as intended. Maintenance is defined as the extent to which the ICT-based centralized monitoring system became part of the standard monitoring system of adherence to immunosuppressive medication in KTRs.

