### Statistical analysis

For categorical data, percent (%) is used for the number of subjects in a category against the total number of subjects. Analysis of categorical data uses the chi-square test or Fisher’s exact test. For continuous data, descriptive statistics (mean and standard deviation (SD)) are given, and the *t* test and the Mann-Whitney *U* test are used for analysis of normal distribution data and non-normal distribution data, respectively. The inter-group difference in adherence to immunosuppressants is assessed with the *t* test. Summary statistics of mean, SD, median, minimum value, and maximum value are presented for measurement data at each visit. The intra-group variation is analyzed with the paired *t* test or Wilcoxon’s signed rank test. Multivariate analysis is performed to identify clinical factors associated with drug compliance. Statistical significance is obtained with a *P* value of < 0.05.

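### The article text names no adherence measure before randomisation and fixes an unadjusted t test; the comparison stays valid but gives up precision, a balance check and a reference for change

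*Protocol article*

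**What the plan says.** **Timing of adherence measurement.** The Study design section states "Both groups are to make six office visits after randomization at 4, 8, 12, 16, 20, and 24 weeks". It then adds that "At each visit, subjects go over the diary with investigators and fill out a questionnaire using the Modified Morisky Adherence Scale". Under Primary outcomes, "pill counts are done at 4, 8, 12, 16, 20, and 24 weeks of follow-up", and the main compliance items "are assessed based on the smart pill box data in the ICT-based centralized monitoring group and the drug administration diary in the ambulatory follow-up group". The Questionnaires section repeats that "Participants in both groups will complete the Modified Morisky Adherence Scale", together with the BMQ-G, but gives no time points.

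**Baseline.** The only assessment that the text explicitly dates to baseline is panel reactive antibody, under Secondary outcomes: "PRA is assessed at baseline and 24 weeks, and serum BK virus at 12 weeks". The full schedule is referred to Fig. 2, which is not reproduced in the text available.

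**Analysis.** The Statistical analysis section names the t test for the between-group difference in adherence and mentions no covariate. It also says that "The intra-group variation is analyzed with the paired *t* test" or a signed rank test, without naming the variables or the reference time point.

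**Language of change.** Under Process evaluation, "Effectiveness is defined as the improvement in adherence to immunosuppressive medication in KTRs". The Study objectives section also plans to relate improved adherence to drug concentrations and to immunological and clinical outcomes.

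**The concern.** Every adherence measurement to which the text gives a time falls after allocation, in an open-label trial. By the week 4 visit the intervention arm has already had about four weeks of alarms and text messages, so no value collected then describes the patients as they entered.

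Three things are at stake:

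- **Precision.** Past adherence plausibly predicts later adherence. An unadjusted t test leaves whatever variance it explains in the error term.
- **Balance.** With 57 patients per arm, a chance difference in prior adherence can be neither seen nor allowed for. The eligibility criteria are broad (age 8 years or older, at least one month after transplantation, no adherence criterion), and the Randomization section describes no stratification by prior adherence.
- **Reference for change.** A paired within-arm test of adherence, or a statement that a patient's adherence improved, needs a value from before the intervention. On the times given in the text, the earliest visit-based value is already under it.

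The Morisky scale suits this purpose because it is already used in both arms and needs neither the device nor a dispensing record. The main compliance items come from different sources in the two arms.

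**Working it through.** **Inputs from the Sample size section:** one-tailed test, alpha 0.05, power 80%, 51 evaluable per arm, 10% dropout, 57 per arm. The section gives no effect size or standard deviation. The document gives no correlation r between a baseline Morisky score and later compliance. Both are assumed below.

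**Step 1: the plan's own figures.** 51 / (1 − 0.10) = 56.7, rounded up to 57, so the dropout step reproduces. The 51 cannot be reproduced without an effect size. Solved backwards, d = (1.645 + 0.842) × √(2/51) = 0.492 by the normal approximation, or 0.496 by the t distribution. An assumed d of 0.50 gives 50 per arm (normal) or 51 (t), so d = 0.50 is a reasonable working value.

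**Step 2: effect of adjustment.** Adjusting for a covariate with correlation r multiplies the residual variance by 1 − r². By the normal approximation:

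- power = Φ( d / (√(1 − r²) × √(2/51)) − z )
- n per arm = 2 × (1 − r²) × (1.645 + 0.842)² / d², one-sided at 80% power

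Here z is 1.645 one-sided and 1.960 two-sided.

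| r (assumed) | 1 − r² | Power at 51 per arm, one-sided | Power at 51 per arm, two-sided | n per arm for 80%, one-sided |
|---|---|---|---|---|
| 0 (unadjusted) | 1.00 | 81% | 71% | 50 |
| 0.2 | 0.96 | 82% | 73% | 48 |
| 0.3 | 0.91 | 84% | 75% | 46 |
| 0.5 | 0.75 | 90% | 83% | 38 |

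For r = 0.3: 0.50 / (0.954 × 0.198) = 2.647; 2.647 − 1.645 = 1.002; Φ(1.002) = 84%. In other terms, 51 adjusted patients per arm act like 51/0.91 = 56 at r = 0.3, or 51/0.75 = 68 at r = 0.5.

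**Step 3: chance imbalance.** With 57 per arm, the standardised baseline difference has standard error √(2/57) = 0.187, so its 95% range is about ±1.96 × 0.187 = ±0.37 SD. An imbalance at that limit shifts the observed contrast by r × 0.37: 0.11 SD at r = 0.3 and 0.18 SD at r = 0.5. Against d = 0.50 that is about 22% and 37%. The t test's error rate already allows for such chance differences on average; adjustment reduces their effect in the trial actually run.

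**The case against.** The strongest objection is that this argues from silence in an incomplete text. Fig. 2 is captioned as the schedule of enrolment, intervention and assessment, and it is not available. The visit paragraph in Study design is demonstrably not a full list: it gives panel reactive antibody only at week 24, while Secondary outcomes adds a baseline value, and it ties eGFR to the follow-up visits although eGFR is an entry criterion. This objection stands. A reader might infer that no baseline Morisky score is taken; the document does not establish that.

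A second objection also stands. The hypothesis is between-group superiority in dose-taking compliance, and a randomised contrast needs no baseline. The improvement named under Process evaluation can be read as that same contrast, and the sentence on paired tests may concern laboratory values. So it would be wrong to say that the efficacy comparison lacks a starting point. That answer is less complete for the Study objectives, where relating improved adherence to outcomes most naturally calls for change within patients.

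Third, the Background itself notes reliability problems with questionnaires, and the Morisky scale is a different instrument from pill-based compliance. The correlation may therefore lie at the low end, and nothing supports calling this score the strongest covariate.

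Fourth, covariates are often left to an analysis plan, which is not shown. That is fair, but the article does name the test for the adherence comparison, and that test is unadjusted.

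Two further inferences fail. The BMQ-G is given no time point, so the text does not show that it is first answered after allocation. Nor is week 4 the start of adherence data: diary and pill box records accrue from the start of follow-up, though still after randomisation.

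**Conclusion.** The point holds in a limited form. The article text names no adherence measure before randomisation and fixes an unadjusted t test. The between-group test is valid; the loss is in precision, in the ability to check balance in prior adherence, and in a pre-intervention reference for any statement about within-arm change.

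The gain in power from adjustment is about 1 to 3 points at r = 0.2 to 0.3 and about 9 points at r = 0.5 (one-sided, 51 per arm, d = 0.50). Both r and d are assumptions, and self-report may put r at the lower end. Whether a baseline score is already collected depends on Fig. 2. The recommendation to adjust does not: if the score exists, using it adds no data collection, and if it does not, obtaining it is cheap.

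**What to change.** 1. Check Fig. 2. If it shows no baseline Morisky score, give the scale once at the existing screening visit, in both arms, before allocation is disclosed. State this in Study design and in Questionnaires.
2. In either case, replace the unadjusted t test for adherence in Statistical analysis with a between-arm comparison of means adjusted for the baseline Morisky score, such as a linear model with arm and that score.
3. Name the baseline Morisky score as the reference for statements about change. It supports change on the Morisky scale itself, not change in pill-based compliance. Say under Process evaluation whether improvement means the between-arm contrast or change within patients, and say under Statistical analysis which variables the paired tests cover and from which time point.

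**Cost:** a few minutes of patient time at a visit that already takes place, and one model term. No added visits or patients are needed. A score not taken before allocation cannot be recovered later. The adjustment does not remove the difference in data source between the arms (pill box against diary), which is a separate matter.

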**Fig. 2 Fig2:**
[figure not shown]
Schedule of enrollment, intervention, and assessment

### Sample size

We hypothesized that the ICT-based centralized monitoring group would be superior to the control group in terms of dose-taking compliance. A one-tailed test with a 0.05 significance level and 80% power provided a size of 51 in each group. With an estimated 10% dropout, the final sample size of 57 was determined (a total of 114 subjects, 57 in each group).

### Study participants

The inclusion criteria are:Patients aged 8 years or olderAt least 1 month lapsing from kidney transplantationStable renal function maintained after kidney transplantation (eGFR ≥ 30 mL/min/1.73 m^2^)History of kidney transplantation only and no other transplanted organsUse of tacrolimus, mycophenolic acid, and steroids for post-transplant immunosuppressionPatients, with the capability and willingness to give consent to trial participation, who have signed the Informed Consent Form in compliance with due process and are capable of making office visits and taking part in the trial as required by the protocol

The exclusion criteria are;Patients’ refusal of the ICT-based centralized home monitoringHistory of treatment for acute rejection within the past 3 monthsActive infectious diseaseUncorrected ischemic heart diseaseVisual or auditory defects that could affect the use of the smart pill boxFingerprint authentication of personal identity deemed impossible (e.g., adermatoglyphia)IlliteracyPatients who do not have phones and cannot receive text messagesOther reasons determined by the investigators that make participation in the clinical trial inappropriate

